## Abstract

**Background:**

Bioimpedance analysis (BIA) has been reported as helpful in identifying hypervolemia. Observation data showed that hypervolemic maintenance hemodialysis (MHD) patients identified using BIA methods have higher mortality risk. However, it is not known if BIA-guided fluid management can improve MHD patients’ survival. The objectives of the BOCOMO study are to evaluate the outcome of BIA guided fluid management compared with standard care.

**Methods:**

This is a multicenter, prospective, randomized, controlled trial. More than 1300 participants from 16 clinical sites will be included in the study. The enrolment period will last 6 months, and minimum length of follow-up will be 36 months. MHD patients aged between 18 years and 80 years who have been on MHD for at least 3 months and meet eligibility criteria will be invited to participate in the study. Participants will be randomized to BIA arm or control arm in a 1:1 ratio. A portable whole body bioimpedance spectroscopy device (BCM—Fresenius Medical Care D GmbH) will be used for BIA measurement at baseline for both arms of the study. In the BIA arm, additional BCM measurements will be performed every 2 months. The primary intent-to-treat analysis will compare outcomes for a composite endpoint of death, acute myocardial infarction, stroke or incident peripheral arterial occlusive disease between groups. Secondary endpoints will include left ventricular wall thickness, blood pressure, medications, and incidence and length of hospitalization.

**Discussions:**

Previous results regarding the benefit of strict fluid control are conflicting due to small sample sizes and unstable dry weight estimating methods. To our knowledge this is the first large-scale, multicentre, prospective, randomized controlled trial to assess whether BIS-guided volume management improves outcomes of MHD patients. The endpoints of the BOCOMO study are of utmost importance to health care providers. In order to obtain that aim, the study was designed with very careful important considerations related to the endpoints, sample size, inclusion criteria, exclusion criteria and so on. For example, annual mortality of Beijing MHD patients was around 10%. To reach statistical significance, the sample size will be very large. By using composite endpoint, the sample size becomes reasonable and feasible. Limiting inclusion to patients with urine volume less than 800 ml/day the day before dialysis session will limit confounding due to residual renal function effects on the measured parameters. Patients who had received BIS measurement within 3 months prior to enrolment are excluded as data from such measurements might lead to protocol violation. Although not all patients enrolled will be incident patients, we will record the vintage of dialysis in the multivariable analysis.

**Trial registration:**

Current Controlled Trials NCT01509937

## Background

Intra-dialytic symptoms are common among patients on maintenance hemodialysis (MHD). Adverse symptoms are associated with both hypervolemia and hypovolemia. Persistent hypervolemia causes hypertension, pulmonary edema, and congestive heart failure, and leads to higher mortality
[1]. Compared with euvolemic patients, patients with recurrent episodes of intra-dialytic hypovolemia are at high risk of accelerated loss of residual renal function
[2], vascular access function loss
[3], brain atrophy
[4], mesenteric infarction
[5], and hence, higher morbidity and mortality
[6,7].

Patients with high pre-dialysis (pre-HD) fluid overload experience higher mortality risk compared with those with less pre-HD fluid burden
[1,8,9]. It is an important strategy to reduce pre-HD fluid burden by restricting inter-dialysis weight gain and to achieve euvolemic (dry) weight post-HD by appropriate ultrafiltration. At present there is no objective gold standard method for estimating target post-HD dry weight and clinical examination is unreliable.

Several observational studies showed that strict post-HD weight control was associated with better short term outcome
[10] or long term survival
[11], but other studies associated strict fluid control with increased morbidity and / or hospitalization
[12,13]. These conflicting results regarding the relationship between fluid control and outcome mainly result from the lack of reliable method for the assessment of individual euvolemia with different studies used different definitions of dry weight including un-tolerated blood volume decrease or ultrafiltration limit
[14].

Bioimpedance spectroscopy (BIS) had long been used to assess human body composition and has been validated by isotope dilution methods
[15,16] and reference body composition methods
[16-18]. Recently, Wizemann et al.
[1] used BIS to assess MHD patients’ fluid status, and found that patients who had 15% or more expansion of extra-cellular fluid (ECF) suffered higher mortality risk compared with those had less than 15% ECF expansion.

BIS appears to be a promising and a valuable tool in aiding dry weight estimation for MHD patients. Although detailed BIS-based dry weight estimating methods were published
[10,19-21], and observational studies showed the potential benefits of BIS
[1,8], it is still not clear whether long-term outcome could be improved by regular dry weight adjustment according to BIS based method.

We designed this multicenter, prospective, randomized and controlled trial to explore the effect of BIS guided fluid management on long-term outcome in MHD patients.

## Methods

### Study design

This is an open label, multicenter, prospective, randomized controlled trial. The aim of the study is to assess if BIS guided fluid management can improve long term outcome in MHD patients. Body composition and hydration state will be assessed with a portable whole body bioimpedance spectroscopy device (BCM—Fresenius Medical Care D GmbH). The study will involve 16 clinical sites, enrolling more than 1300 participants. The enrolment period will last approximately 6 months, with a planned minimum 36 months follow-up period. Participants will be randomized to two arms, the control arm and BCM arm. Patients in both arms will receive BCM measurement, but results from the BCM measurement in the control group will be kept blinded to the investigators. Participants in control group will be followed up and their dry weights will be adjusted according to the dialysis center’s standard clinical practice. Clinicians managing participants in the BCM group, in addition to routine practice, will receive BCM measurement and dry weight will be adjusted according to BCM output data estimating overhydration and dry weight. All of baseline demographics, clinical data, laboratory data, regular BCM measurement, and ultrasonic cardiograph (UCG) data will be recorded on study case report forms (CRFs).

The flow chart of the study is shown in Figure
1.

**Figure 1 F1:**
[figure not shown]
BOCOMO study Flow chart.

### Study objectives

The objective of the study is to characterize the benefit of BCM guided fluid management in MHD patients.

#### Primary objective

The primary objective of the study is to compare incidence rate of a composite endpoint between BCM group and control group. Participants reach the primary endpoint if at least one of the following occurs: (1) death, (2) acute myocardial infarction, (3) cerebral thrombosis, (4) cerebral hemorrhage, (5) peripheral arterial occlusive disease. The diagnosis of endpoints will be made by the Endpoint Committee.

#### Secondary objectives

Secondary objectives are to compare the following indices between BCM arm and control arm: (1) left ventricular thickness and left ventricular ejection fraction, (2) Pre-HD and post-HD blood pressure, (3) anti-hypertensive medication, (4) hospitalization rate.

### Study protocol

#### Inclusion criteria

Candidates must meet all of the following criteria to be eligible for enrollment into the study: (1) diagnosis of end stage renal disease (ESRD) and need for MHD, (2) age of 18 to 80 years old, (3) on MHD for at least 3 months, (4) dialysis frequency of at least 5 sessions per 2 weeks, not less than 4 hours per session and Kt/V at least 1.2, (5) urine volume less than 800 mL per 24 hours the day before dialysis session, (6) BIS not used within recent 3 months, (7) dry weight regarded as adequate according to the patient’s responsible doctor, (8) the ability to understand and willingness to sign an informed consent statement.

#### Exclusion criteria

Candidates meeting any one of the following criteria will not be eligible to be included in the study: (1) acute infection within prior month, (2) active rheumatic disease, or current receipt of cortical steroid or cytotoxic medication, (3) uncontrolled neoplasm, (4) acute myocardial infarction within prior month, (5) congestive heart failure (NYHA 3 – 4), (6) stroke within 3 prior months, (7) metallic prosthesis (contraceptive device, artificial joint), (8) amputation, (9) female of childbearing age who has a pregnancy plan, or is pregnant, or is breast feeding, (10) having a plan to reduce dialysis frequency, (11) having a renal transplantation plan or planning to transfer to peritoneal dialysis within 3 years, (12) participating or planning to participate in other clinical trials which would confound the current study.

Candidates meeting inclusion and exclusion criteria will be included in the study after providing informed consent. Study approval is obtained from the Institutional Review Board, Peking University First Hospital. This study is registered on ClinicalTrial.gov and has the identification number NCT 01509937.

#### Data collection

Summary of data collection is listed in Table
1.

**Table 1 T1:** BOCOMO study schedule of data collection

**Item**	**Baseline frequency**	**Follow up frequency**
Demographic information	Once	-
ESRD history^1^	Once	-
Comorbidity^2^	Once	-
Physical examination^3^	Once	Every 2 months
Timed urine collection^4^	Once	Every 2 months
CBC^5^	Once	Every 3 months
Routine laboratory data^6^	Once	Every 3 months
Kt/V	Once	Every 3 months
iPTH	Once	Every 3 months
hsCRP	Once	Every 3 months
UCG	Once	Every 12 months
BCM measurement	Once	Every 2 months in BCM arm
Dialysis prescription change^7^	Once	Throughout the study period
Medication change^8^	Once	Throughout the study period
New clinical event^9^	-	Throughout the study period

Abbreviation: BOCOMO study, body composition monitor study; ESRD, end stage renal disease; CBC, complete blood count; Kt/V, calculated using Daugirdas single pool equation; iPTH, intact parathyroid hormone; hsCRP, high sensitive C-reactive protein; UCG, ultrasonic cardiograph.

^1^ESRD history includes cause of ESRD, date of first dialysis, type of vascular access.

^2^Detailed history of comorbidity will be assessed, including vascular access events.

^3^Physical examination includes body weight, blood pressure, heart rate, edema, pulmonary rale, before and after hemodialysis session.

^4^24 hours urine volume collected the day before dialysis session will be recorded.

^5^Consists of hemoglobin, white blood cell count, platelet count.

^6^Consists of albumin, pre-Albumin, creatinine, urea, potassium, sodium, chloride, calcium, phosphate, bicarbonate, alkaline phosphatase (ALP), glucose, triglycerides, total cholesterol, low density lipoprotein, high density lipoprotein, brain natriuretic peptide (BNP).

^7^Any dialysis prescription change throughout the study period will be recorded.

^8^Any medication change throughout the study period will be recorded.

^9^Any new clinical event throughout the study period will be recorded, including hospitalization, new diagnosis, vascular access related event, treatment of abnormal laboratory value, dry weight adjustment.

##### Baseline data collection

In brief, baseline data are collected before initiation of BCM monitoring and include demographics, ESRD treatment history, current vascular access type, detailed comorbid conditions assessment, current dialysis prescription and medications (oral, subcutaneous and intravenous), CBC, routine laboratory data, Kt/V, iPTH and hsCRP. UCG will also be performed. BCM measurement will be done in participants in both BCM arm and control arm. In the control arm, BCM data will not be provided to patient care provider. 24 hours urine volume will be recorded the day before dialysis session. A physical examination will be performed.

##### Follow up data collection

Physical examination and urine volume collection will be performed every 2 months. CBC, routine laboratory data, and Kt/V will be obtained every 3 months. iPTH and hsCRP will be measured every 3 months. UCG will be performed every 12 months.

BCM measurement will be performed every 2 months in BCM arm, data will be recorded and provided to the care provider.

#### Dry Weight Adjustment Strategy

All participants will be educated to reduce inter-dialysis weight gain to less than 5% body weight.

For participants in the control arm, dry weight will be adjusted according to the clinical site’s standard clinical practice.

For participants in the BCM arm, dry weight will be adjusted according to the BCM estimates of overhydration and normovolemic weight. During each dialysis session, participants’ dry weight will be increased or decreased toward BCM reported dry weight. The increment or decrement of dry weight will not be greater than 0.5 Kg within a single dialysis session. Thus, in this arm participants’ dry weights will be gradually adjusted to BCM reported value. If ultrafiltration is not tolerated because of hypovolemia based on symptoms and signs, such as muscle cramps, need for excessive saline, or symptomatic hypotension, adverse events will be recorded, and the actual dry weight will be adjusted by plus 0.5 Kg. If participants experience hypervolemic clinical episodes, such as hypertension related symptom, congestive heart failure, pulmonary edema, adverse events will also be recorded. If a patient experiences the same adverse effect of dry weight change for two consecutive visits, the patient will be removed from the study because of adverse event.

Dry weight adjustment flow chart in the BCM arm is shown in Figure
2.

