#### Clinical events

##### Dialysis prescription change

Dialysis prescription may be changed according to clinical site’s standard practice including changes of dialyzer, blood flow rate, dialysate flow rate, frequency of dialysis, dialysis modality (conventional hemodialysis, high flux dialysis, hemofiltration, hemodiafiltration, and in combination of blood perfusion). Kt/V will remain not less than 1.2 despite dialysis prescription change. Dialysis prescription change is regarded as a clinical event and will be recorded.

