#### Analytical method

##### Primary endpoint

The primary analysis will be an intent-to-treat analysis comparing composite endpoint between the BCM and the control arms. The intent-to-treat population is defined as all enrolled study participants. For this analysis, the follow-up time begins from the enrollment date to the composite endpoint, loss to follow-up, or end of study.

Multivariate Cox proportional hazards regression models will be used for analysis of the risk of death comparing BCM and control arms, with adjustment for age, sex, dialysis vintage, primary cause of ESRD, comorbid conditions, and other characteristics that may be associated with increased risk of death, such as inter-dialysis weight gain, hypertension and hsCRP.

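### Control care is set by each of 16 sites, yet site is not named in the Cox adjustment or the secondary comparisons: a small efficiency loss on the primary endpoint, and possibly an understated variance for hospitalization

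*Protocol article*

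**What the plan says.** Under Dry Weight Adjustment Strategy: "For participants in the control arm, dry weight will be adjusted according to the clinical site’s standard clinical practice". Under Study design: "The study will involve 16 clinical sites, enrolling more than 1300 participants". Other background care also follows the site, in both arms. Under Dialysis prescription change: "Dialysis prescription may be changed according to clinical site’s standard practice". Medications change says the same for drugs. The intervention arm keeps this background too: "Clinicians managing participants in the BCM group, in addition to routine practice, will receive BCM measurement".

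On allocation, the abstract says only: "Participants will be randomized to BIA arm or control arm in a 1:1 ratio". On the primary analysis: "The primary analysis will be an intent-to-treat analysis comparing composite endpoint between the BCM and the control arms". The one model named in that section is a multivariable Cox regression, worded for the risk of death. Its covariates are stated in these terms: "with adjustment for age, sex, dialysis vintage, primary cause of ESRD, comorbid conditions, and other characteristics". Three examples of such further characteristics follow: weight gain between sessions, hypertension and hsCRP. Site is not mentioned.

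The Secondary endpoint section fixes a two-group t-test for the echocardiographic, blood pressure and antihypertensive endpoints, and a Poisson regression for the hospitalization rate. Neither is stated with site.

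**The concern.** Usual care here is whatever each centre does about dry weight, prescription and drugs. Site is therefore a variable that the design itself makes likely to affect event rates, blood pressure, echo findings and admissions. The article does choose adjustment variables, and every one it names is a patient characteristic.

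The consequence depends on the analysis:

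- **Cox model.** Pooling sites with different baseline risks gives a marginal hazard ratio that lies nearer 1 than the within-site ratio, with some loss of power.
- **Poisson model.** Unmodelled site differences are extra variation that the Poisson variance does not contain, so the standard error can be too small.
- **t-tests.** Site variation stays in the residual, which costs power or, if allocation was balanced within sites, makes the test conservative.

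**Working it through.** **Inputs from the article.** 16 sites. Three-year composite rates of 40% (control) and 32% (BCM). Alpha 0.05, power 80%, 1128 patients before and 1354 after the allowance for loss (Sample size calculation). **Not given:** between-site spread, mean number of admissions, intraclass correlation. These are assumed below and shown as ranges.

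**1. The plan's own figure.** Two proportions, 0.40 vs 0.32, two-sided 0.05, power 80%, pooled variance, no continuity correction: 564 per arm, 1128 in total. This matches the article. The implied hazard ratio is ln(0.68)/ln(0.60) = 0.755.

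**2. Composite, Cox model with and without site.** Normal site effect on the log hazard, exponential times calibrated to a 40% control risk at 36 months, within-site hazard ratio 0.755, N = 1128, 16 sites, individual 1:1 allocation not balanced by site. The hazard ratio column is the large-sample limit without site. The power columns come from 10,000 simulated trials per row.

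| Assumed site SD | Site 3-year control risk, ±2 SD | HR without site | Power without site | Power, stratified by site |
|---|---|---|---|---|
| 0 | 40% | 0.755 | 80.1% | 79.3% |
| 0.2 | 29% to 53% | 0.757 | 80.2% | 79.9% |
| 0.3 | 24% to 60% | 0.759 | 78.4% | 78.7% |
| 0.4 | 20% to 67% | 0.762 | 78.4% | 80.1% |
| 0.5 | 16% to 73% | 0.766 | 76.7% | 80.2% |

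A separate run of the same comparison gave 80.9% vs 80.9% (SD 0.2), 79.7% vs 80.4% (SD 0.3) and 78.8% vs 80.3% (SD 0.4). The gain from stratifying is thus about 0 to 1.5 points for SD 0.2 to 0.4, with simulation noise of a few tenths of a point. It is about 3.5 points at SD 0.5. If sites did not differ at all, stratifying would cost about 0.8 points. The attenuation of the log hazard ratio is 0.8%, 1.9% and 3.3% at SD 0.2, 0.3 and 0.4.

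With no treatment effect, 2000 simulated trials per setting gave a mean log hazard ratio of about 0. Type I error without site was 3.9% to 5.7%, much the same as with strata.

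**3. Hospitalization, Poisson model without site.** With mean count m and a log-normal site effect, allocated independently of site, the ratio of true to Poisson variance is 1 + m(exp(SD²) − 1). The actual type I error is 2[1 − Φ(1.96/√ratio)].

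| Assumed SD | Mean stays m | exp(SD²) − 1 | Variance ratio | Type I error |
|---|---|---|---|---|
| 0.3 | 1.5 | 0.0942 | 1.141 | 6.7% |
| 0.4 | 1.5 | 0.1735 | 1.260 | 8.1% |
| 0.3 | 3 | 0.0942 | 1.283 | 8.4% |
| 0.4 | 3 | 0.1735 | 1.521 | 11.2% |

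Simulation (1354 patients, 16 sites, simple 1:1 allocation, 8000 trials) agrees: 6.3%, 7.7%, 7.9% and 10.5% in the same order, against 4.5% to 5.1% with site in the model. If allocation was balanced within sites, the site component cancels from the arm difference and this inflation disappears.

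**4. t-tests.** With intraclass correlation ρ and unbalanced allocation, power falls from 80% to Φ(2.80√(1 − ρ) − 1.96): 78.0% at ρ = 0.05 and 75.7% at ρ = 0.10. With allocation balanced within sites, the unadjusted test has a true level of 2[1 − Φ(1.96/√(1 − ρ))]: 4.4% and 3.9%.

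**5. Patients per site.** 1354/16 = 84.6. Events per site at the planned rates: 84.6 × 0.36 = 30.

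**The case against.** Several points on the other side stand.

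- **No bias in the primary comparison.** A reader might infer that site differences confound the treatment effect. They do not: individual randomisation balances site in expectation, and the simulated type I error is unaffected. The shift in the hazard ratio is non-collapsibility, a marginal rather than a within-site ratio.
- **The Cox sentence does not exclude site.** It is worded for death, the composite comparison has no named model, and the covariate list is open-ended. It would be too strong to say that the primary model leaves site out. What can be said is that a list was given and site is not on it, and that the examples for the open part are all patient characteristics.
- **Allocation is simply not described.** A reader might infer that arms are unbalanced within sites. A 1:1 ratio is compatible with blocks within site, and an article commonly leaves this to the full protocol.
- **The spread is unknown and may be small.** The article says that most sites are in Beijing, and all patients meet common minimum criteria on dialysis frequency, session length and Kt/V.
- **Strata do not answer heterogeneity of effect.** If usual care differs by site, the contrast with BCM guidance may differ too, and a common-effect stratified model does not examine that.

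The objection that all of this belongs in an unseen analysis plan succeeds for allocation but not for the analysis. The article itself names the adjustment variables and specifies the t-test and the Poisson regression.

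**Conclusion.** The point holds in a limited form. Site defines the control care but is not named in the adjustment set or the secondary analyses. The primary comparison remains valid. The cost there is a hazard ratio of about 0.757 to 0.762 instead of 0.755 and about 0 to 1.5 points of power, for an assumed site SD of 0.2 to 0.4. A larger loss needs spreads for which the article gives no evidence.

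The hospitalization analysis is the more exposed. A plain Poisson model without site would have a type I error of about 6.7% to 11%, provided that allocation was not balanced within sites, that the site SD is 0.3 to 0.4 and the mean is 1.5 to 3 stays, and that no variance correction is specified elsewhere. None of these conditions can be verified from the article.

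**What to change.** - **Analytical method, Primary endpoint:** state that the Cox model for the composite endpoint is stratified by clinical site, with a separate baseline hazard per site and a common treatment effect.
- **Secondary endpoint:** include site in the blood pressure, echocardiographic and antihypertensive medication comparisons (a linear model with arm and site in place of the plain t-test), and in the hospitalization model.
- **Allocation:** confirm whether it was balanced within sites. The analysis change is worth making either way.

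The cost is a few words of analysis text, with no new data and no change to patient care. With about 85 patients and 30 events per site, the loss of information is negligible: under one point of power even if sites do not differ at all. The change should be made before outcome data are seen by arm. It does not address a treatment effect that varies between sites, which would need its own assessment.

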##### Data censoring

The following participants are censored: (1) transfer to peritoneal dialysis, (2) renal transplantation, (3) becomes pregnant, (4) receives metal implantation, or any other reasons that make BCM measurement impossible, (5) limb amputation, (6) withdrawal of consent, (7) receives any forms of BIS measurement other than those specified by the trial protocol, (8) relocates to other clinical site, (9) investigator requests the participant be withdrawn from the study.

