### Dry weight adjustment in BCM arm

“Real dry weight” is unknown in BOCOMO study. BCM reported dry weight might by significantly higher or lower than the real dry weight, which will lead to hypervolemia related acute symptoms and hypovolemia related acute symptoms, respectively. They will also worsen patients’ long-term outcome. In these kinds of conditions, adverse events attributes to BCM arm will be recorded.

Another issue regarding dry weight adjustment in BCM arm is the amount of each dry weight increase or decrease. Large amount of dry weight change is not allowed because significant dry weight increase or decrease during one HD session will lead to dramatic blood volume increase or decrease during HD session and associated clinical manifestation.

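### The BCM-arm rule that removes patients from the study after a repeated dry-weight adverse effect does not reconcile with the intent-to-treat follow-up or the censoring list, and can lose later events mainly from one arm

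*Protocol article*

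**What the plan says.** All references are to the protocol article.

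- **Dry Weight Adjustment Strategy, control arm.** One sentence: "For participants in the control arm, dry weight will be adjusted according to the clinical site’s standard clinical practice". No removal rule follows it.
- **Same section, BCM arm.** A separate paragraph opens with "For participants in the BCM arm, dry weight will be adjusted according to the BCM estimates of overhydration and normovolemic weight". It describes the stepwise adjustment, says that hypovolemic and hypervolemic adverse events are recorded, and ends with the rule: "If a patient experiences the same adverse effect of dry weight change for two consecutive visits, the patient will be removed from the study".
- **Analytical method, Primary endpoint.** "The intent-to-treat population is defined as all enrolled study participants", and "the follow-up time begins from the enrollment date to the composite endpoint, loss to follow-up, or end of study".
- **Data censoring.** Nine reasons are listed. A repeated dry-weight adverse effect is not among them. The only item that could absorb it is the ninth: "investigator requests the participant be withdrawn from the study".
- **Discussions, Dry weight adjustment in BCM arm.** The BCM dry weight may be too high or too low. This causes acute symptoms, and "They will also worsen patients’ long-term outcome".
- **New diagnosis** and **Interim analysis.** Hypotensive and hypertensive episodes are recorded as clinical events with no restriction to an arm. The study may stop early if fluid-related adverse events are significantly high in the BCM arm.

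**The concern.** The wording takes the patient out of the study, not merely out of BCM-guided adjustment. A site that follows it literally would stop collecting outcomes. Patients who meet the rule have reacted badly to the intervention under test, and the article itself links the cause of that reaction to a worse long-term course. If their later deaths, infarctions, strokes and arterial occlusions go uncollected in the BCM arm, while comparable control patients stay under observation, the comparison tilts towards BCM.

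This is more than detail that an analysis plan could supply. The article states an explicit rule that its own primary analysis does not accommodate, and no analysis plan can recover outcomes that were never collected.

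**Working it through.** **1. Setting the sections side by side**

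| Question | Dry Weight Adjustment Strategy | Data censoring | Primary endpoint |
|---|---|---|---|
| Does the patient leave? | Yes, the study | Not named; only item 9 could cover it | Not a stopping point |
| Which arm? | Placed in the BCM paragraph | Both arms | Both arms |
| Does outcome follow-up continue? | Not stated | Not stated | Implied, since only endpoint, loss or study end stops it |

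One section takes the patient out, a second does not say how to treat this, and the third assumes that it does not happen.

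**2. The plan's own figure**

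Inputs from Sample size calculation: 40% against 32% at 3 years, α 0.05 (taken as two-sided), power 80%; mean rate 0.36. Per arm, with pooled variance under the null:

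n = [1.960 × √(2 × 0.36 × 0.64) + 0.842 × √(0.40 × 0.60 + 0.32 × 0.68)]² / 0.08² = (1.330 + 0.569)² / 0.0064 ≈ 564

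The total is 1128, as stated. The corresponding planned hazard ratio is ln 0.68 / ln 0.60 = 0.755.

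**3. Upper-end bias: removal at or near baseline**

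The removed share f and the risk ratio k (removed against retained patients) are assumptions; the article gives neither. With no true effect (40% in both arms), the risk among retained BCM patients is r = 0.40 / (1 − f + fk).

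- f = 5%, k = 1.5: 0.40 / 1.025 = 39.0%, a spurious gain of 1.0 point
- f = 10%, k = 1.5: 0.40 / 1.05 = 38.1%, 1.9 points
- f = 10%, k = 2: 0.40 / 1.10 = 36.4%, 3.6 points, or 45% of the planned 8 points
- k = 1: no bias at any f

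**4. Time-to-event simulation**

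Assumptions: no true effect, 677 patients per arm (1354 / 2), exponential event times with 40% overall 3-year risk, and the same share of higher-hazard patients in both arms. Those in the BCM arm are censored at a uniformly distributed time. There were 2000 to 3000 trials per scenario, and ranges are over repeat runs. The last figure in each cell is the chance of a significant result favouring BCM, nominally 2.5%.

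| Removed, hazard ratio | Removal over first 8 months | Removal over 36 months |
|---|---|---|
| 5%, 1.5 | HR 0.98; 3.5-4.0% | HR 0.99; about 3% |
| 5%, 2 | HR 0.97; about 6% | HR 0.98; about 4% |
| 10%, 1.5 | HR 0.96; 6-7.5% | HR 0.98; about 4% |
| 10%, 2 | HR 0.94; 9-12% | HR 0.97; 5-5.5% |

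At 2% removed, 1.5 times the hazard and early removal, the HR is 0.99 with about 3%. When the same patients are followed to the end, the HR returns to 1.00 and the rejection rate to about 2.5%.

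**The case against.** The strongest reply is that the primary analysis, read literally, already keeps these patients. All enrolled participants are in the population, removal is not a stopping point, and the censoring list does not name it. That much stands: a reader might infer that the plan deletes BCM failures from the primary comparison, and the text does not establish this. The reply does not settle the matter, because an analysis can use only what is collected, and nothing says that collection continues after a patient is removed from the study.

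Other points stand as limits:

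- **Arm restriction.** The rule speaks of a patient in general. That it covers only the BCM arm is inferred from its place and trigger. The article does not say what happens to a control patient with the same symptoms, and the BCM flow chart is not reproduced.
- **Hidden harm.** A reader might infer that the rule conceals harm. It does not conceal the adverse events: they are recorded before removal, attributed to the BCM arm, and feed a stopping criterion. Only composite events after removal are at risk.
- **Control-arm recording.** It would be wrong to say that fluid-related events go unrecorded in controls, because the New diagnosis section covers most of them without regard to arm.
- **Persistence of excess risk.** The Discussions tie the worse outcome to a wrong dry weight. They do not say that the excess risk lasts once BCM guidance stops.
- **Timing.** BCM measurement is repeated every 2 months throughout, so removals need not cluster early. Spreading them over 36 months roughly halves the bias.

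**Conclusion.** The point holds as a failure to reconcile three sections, with a real risk of losing outcome data mainly from the BCM arm. The likely direction favours BCM, because the article expects patients with a wrong BCM dry weight to do worse.

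The size cannot be fixed from the document. Removal rate, excess hazard and timing are all assumed here. For 5-10% removed at 1.5-2 times the hazard, the apparent HR under no effect is about 0.94-0.98 with early removal and 0.97-0.99 with removal spread over follow-up, against a planned 0.755. The chance of a false significant benefit is about 4-12% and 3-5.5% respectively, instead of 2.5%. The bias could be negligible. It still warrants correction, because the remedy is cheap and uncollected outcomes cannot be restored at analysis.

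**What to change.** Reconcile Dry Weight Adjustment Strategy, Data censoring and Primary endpoint by stating that:

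1. a patient who meets the repeated-adverse-effect rule remains in follow-up for every component of the composite until end of study, whatever the care team decides about dry weight;
2. the patient is analysed in the randomised arm;
3. meeting this rule, including by way of investigator-requested withdrawal, is not a censoring reason in the primary analysis.

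Also confirm that the fluid-related events already recorded under New diagnosis are captured in the same way in both arms, so that the adverse-event criterion under Interim analysis compares like with like.

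The clinical rule on dry weight is not touched and stays with the clinical team.

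The cost is protocol wording and a little more follow-up, modest for patients who still dialyse at the study site. Keeping patients who have left BCM guidance slightly dilutes the treatment contrast. If they are followed and analysed as randomised, this rule introduces no bias and leaves the 1128 calculation as it stands.
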